12.2 Source Documents and Source Data

Source documents are original documents, data and records of clinical findings, observations and other activities in a clinical study necessary for the reconstruction and evaluation of the study. Source documents will include: all logs and notes from the study site, laboratory records specific to this study and relevant: hospital records, clinical and office charts, laboratory notes, memoranda, evaluation checklists, pharmacy dispensing records, recorded data from automated instruments, copies or transcriptions certified after verification as being accurate copies, microfiches, photographic negatives, microfilm or magnetic media, x-rays, subject files and records kept at the pharmacy, at the laboratories and at medical/technical departments involved in the clinical study.

12.3 Confidentiality of Data and Access to Subject Records

Data collected during this study will be used to support the development, registration and future marketing of H5 VLP (H1N1) pandemic influenza vaccine. All data collected during the study will be controlled by the Sponsor or designee and the Sponsor will abide by all relevant data protection laws. After subjects have consented to take part in the study, their medical records and data collected during the study will be reviewed by representatives of the Sponsor and / or the company organizing the research on the Sponsor’s behalf to confirm that the data collected is accurate and for the purpose of analyzing the results. These records and data may additionally be reviewed by auditors, interested commercial parties or by regulatory authorities. The subject’s name, however, will not be disclosed outside the clinical site but rather by a unique subject number. The results of this study may be used in submissions to other countries throughout the world, which have ensured an adequate level of protection for personal data.

To ensure compliance with relevant regulations, data generated by this study must be available for inspection upon request by the Sponsor or an authorized representative of Medicago R&D Inc., regulatory authorities and the IRB/IEC.

12.4 Monitoring, Auditing and Archiving

12.4.1 Monitoring

The study will be monitored by representatives of Medicago R&D Inc. throughout its duration by means of personal visits to the Investigator’s facilities and other communications. Monitoring visits by Medicago R&D Inc should be scheduled at mutually agreeable times periodically throughout the study. These visits will be conducted to evaluate the progress of the study, verify the rights and well-being of the subjects are protected, verify the reported clinical study data are accurate, complete and verifiable from source documents, and the conduct of the study is in compliance with the approved protocol and amendments, GCP and applicable regulatory requirements. A monitoring visit should include a review of the essential clinical study documents (regulatory documents, CRFs, source documents, drug disposition records, subject informed consent forms, etc.) as well as discussion on the conduct of the study with the Investigator and staff.

The Study Monitor should conduct these visits as frequently as appropriate for the clinical study. The Investigator and staff should be available during these visits to facilitate the review of the clinical study records and resolve/document any discrepancies found during the visit.

12.4.2 Audits and Inspections

In accordance with the principles of GCP, the study may be inspected by regulatory authorities, the Sponsor or assigned designee. The Sponsor is entitled to access information about the status of the study and to review the original study documents or site documents supporting the study.

During the course of the study, Quality Assurance auditors may audit the investigational site. As Medicago R&D Inc representatives, they are entitled to access all subject and study information, excluding the randomized treatment assignments.

12.4.3 Archiving

The Investigator will retain the source documentation including: the original informed consent forms, study documentation (e.g. IRB/IEC approval letters, etc.) and a copy of the completed CRFs for 25 years as per Canadian Food and Drug Regulations; Part C, Division 5, Section C.05.012 (3) (h). After 25 years, the Investigator must contact Medicago R&D Inc. prior to the disposal of any study documents (Adopted from ICH guidelines, GCP, Section 4.9.5). If before the 25 year retention period is completed, the Investigator or institution can no longer maintain the study documentation, Medicago R&D Inc. should be contacted to make other arrangements for storage.

12.5 Financial Contract and Insurance Coverage

Medicago R&D Inc. has suitable insurance to cover clinical trials and product liability. The Investigator site has suitable insurance to cover negligence and default liability.

12.6 Stipends for Participation

Subject stipends for clinical trial participation must be clearly outlined in the Informed Consent Form and approved by the IEC/IRB.

**APPENDIX A – SAMPLE MEMORY AID – Day 0 – Day 7 (Page 1 of 4)**

| **Protocol: CP-H5VLP-001 Memory Aid (MA)** | | **Subject ID No. and Subject Initials:** | **PM, Day 1 Of Dose** | **1 Day after** | **2 Days after** | **3 Days after** | **4 Days after** | **5 Days after** | **6 Days after** | **7 Days after** |
| --- | --- | --- | --- | --- | --- | --- | --- | --- | --- | --- |
| **DAILY TEMPERATURE** | | **Record your oral temperature here (degrees Celsius) ►** |  |  |  |  |  |  |  |  |
| **Fill in today’s column by entering the WORST grade for each symptom that you have had in the last day (24 hours).** | | | | | | | | | | |
| **SYMPTOMS** | | **If you did not have the symptoms, enter “0”** | **PM, Day 1**  **Of Dose** | **1 Day after** | **2 Days after** | **3 Days after** | **4 Days after** | **5 Days after** | **6 Days after** | **7 Days after** |
| ► | Redness where the injection was given | 0 = None 1= More than 0 but NOT more than 20 mm 2= More than 20 mm but NOT more than 50 mm 3= More than 50 mm |  |  |  |  |  |  |  |  |
| ► | Swelling where the injection was given |  |  |  |  |  |  |  |  |  |
| ► | Pain where the injection was given | 0 = None 1= More than 0 but NOT more than 20 mm 2= More than 20 mm but NOT more than 50 mm 3= More than 50 mm |  |  |  |  |  |  |  |  |

|  | **APPENDIX A - Sample Memory Aid – Day 0 – Day 1 (page 2 of 4)** | | | | | | | | | |
| --- | --- | --- | --- | --- | --- | --- | --- | --- | --- | --- |
| ► | Headache | 0 = None  1 = Mild - Noticeable, but doesn’t interfere with my work / normal activities.  2 = Moderate - Bad enough to limit my work / normal activities.  3 = Severe - Bad enough to prevent my work / normal activities |  |  |  |  |  |  |  |  |
| ► | Muscle aches |  |  |  |  |  |  |  |  |  |
| ► | Joint aches |  |  |  |  |  |  |  |  |  |
| ► | Fatigue |  |  |  |  |  |  |  |  |  |
| ► | Chills |  |  |  |  |  |  |  |  |  |
| ► | Feelings of general discomfort or uneasiness |  |  |  |  |  |  |  |  |  |
| ► | Swelling in the axilla (*R/L) |  |  |  |  |  |  |  |  |  |
| ► | Swelling in the groin (R/L) |  |  |  |  |  |  |  |  |  |
| ► | Swelling in the neck |  |  |  |  |  |  |  |  |  |
| ► | Swelling in the chest |  |  |  |  |  |  |  |  |  |
| **Please report any other problem not listed above to the Study Investigator.**  **Symptoms listed above which persist after the time of this 7- day telephone contact should be considered as an adverse event.** | | | | | | | | | | |

*R = Right

*L = Left

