5.1.5.3 Minimum 2-hour Post-Dose Observation Period

- Subjects will remain in clinic for at least 2 hours post-vaccination.
- During the observation period in clinic, vital signs (BP, HR, RR and oral temperature will be taken/assessed hourly. Any unusual signs or symptoms reported during the initial 2 hours of observation will prompt continued close monitoring All data will be recorded in the source document during the post observation period.
- During the observation period, subjects will be provided a Memory Aid (MA), a template for measuring solicited local reactions and an oral digital thermometer to record daily temperature in degrees Celsius. The clinic staff will provide training to the subjects during this time. The subjects will be:
  - Instructed on how to measure their oral temperature with the digital thermometer supplied to them for purposes of the study. From the evening of Day 0 to Day 7 following each vaccination, temperature will be taken at approximately the same time each evening and the findings will be recorded in the MA.
  - Instructed by study staff on how to measure erythema (redness) and swelling 0-20 mm, 21-50 mm and > 50 mm diameter at the injection site using the simple template supplied and to evaluate pain at the injection site. Local tolerance reactions will be assessed every day starting from the evening the injection was administered on Day 0 and continuing and up to Day 7 following each vaccination and recorded on the MA.
  - Requested to grade, on a daily basis from the evening of Day 0 through to Day 7 following each vaccination, each of the solicited systemic reactions as described in Appendix A, the MA.
  - Requested to record their individual data in their MA as described above
  - Requested to use their MA to support their recall in providing information during the scheduled telephone interview conducted on Days 1 and 8 following each vaccination
  - Advised that they will be asked about the occurrence of any symptoms or events requiring medical attention and the use of concomitant medication during each 21-day post dose period as well as throughout the 160 day follow-up period
  - Requested to bring their MA to each clinic visit. The completed MA will not be collected by the study site.

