  - Advised on emergency contact information and instructions for contacting study personnel. Subjects will be advised to immediately contact the Investigator, or his designee, in the event of a serious adverse event or medical emergency. Subjects will be provided with a telephone contact number and be instructed to call if any reaction to vaccination is significant or concerning.
  - Advised to notify their health care professional(s) (e.g., primary care physician) that they are participating in a clinical research study of an influenza vaccine.
  - Provided with a date and time to return to the clinic for the Day 21 and Day 42 follow-up visits.

5.1.5.4 Days 1 and 8 Telephone Contact (acceptable interval +/- 1 day), following vaccination 1 and 2)

- Subjects will be asked to use their MA to support their recall in providing information during the scheduled telephone interview conducted on Days 1 and 8 following each vaccination
- Telephone calls will be conducted at Days 22 and 29 (one and eight days following the second vaccination).
- The highest oral temperature, the greatest dimension of local redness and swelling, and the highest symptom grade experienced for each solicited local and systemic reaction from Day 0 to Day 1 and Day 2 – Day 7, will be ascertained and recorded.
- Unsolicited adverse events and/or solicited local and systemic reactions of greater than (>) grade 2 (moderate) severity will be reported promptly (24-48 hours) to the Investigator, who may request the subject come to the clinic for evaluation at his/her discretion. The Investigator will document review of these AEs on the source document.
- If any of the solicited local or systemic reactions noted at the Day 8 telephone contact persist beyond Day 7, these will be considered an AE. The subject will be requested to note when the AEs resolve and report this information to the Investigator or clinic staff at the Day 21 or Day 42 visit.
- Subjects will also be asked about any difficulties in completing the MA, any change in health, any visits to health care facilities and / or medical practitioners and use of any concomitant medications

The subject will be reminded of the date and time of their Day 21 and Day 42 visits.

- - - 1. Day 21 Visit, second vaccination, (acceptable interval +/- 2 days) and

Day 42, (acceptable interval +5 days)

The following procedures will be performed:

- Oral temperature in ºCelsius will be taken and recorded.

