8.0 ASSESSMENTS METHODS AND ENDPOINTS

8.1 Safety Endpoints, Immunogenicity Endpoints, and Assessments Methods

8.1.1 Endpoints

8.1.1.1 Primary Endpoints

Safety and tolerability endpoints to be collected include solicited symptoms, oral temperature and local injection site pain, erthyema (redness) and swelling. Systemic complaints reasonably anticipated to occur as a result of receipt of the test articles will be graded as mild, moderate or severe as follows: headache, muscle aches, joint aches, fatigue, chills, feelings of general discomfort, or uneasiness, swelling in the axilla, groin, neck or chest. These signs and symptoms will be measured and reported by each study subject from the time of study vaccine administration to (Day 0 – Day 1 and Day 2 – Day 7) seven days post-vaccination.

- - Percentage, intensity and relationship of immediate complaints for at least 2 hours post-vaccination)
  - Percentage, intensity and relationship to vaccination of solicited local and systemic signs and symptoms 7 days following each dose of study vaccine
  - Percentage, intensity and relationship of solicited and unsolicited local and systemic signs and symptoms 21 days following each dose of study vaccine
  - Occurrence of all adverse events and serious adverse events
  - The number and percentage of subjects with normal and abnormal haematological and biochemical values at Screening, Day 21 and 42
  - The number and percentage of subjects with normal and abnormal urine values at Screening, Day 21 and 42

Any adverse events or serious adverse event will be collected throughout the course of the study. The collection of adverse events will begin following the signature of the Informed Consent Form.

Any clinical laboratory test result that meets the criteria for an AE in the absence of appropriate and/or adequate clinical diagnosis should be reported as an A/E, unless the result is considered normal for the current trial subject population.

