**APPENDIX B – SAMPLE TELEPHONE FOLLOW-UP SCRIPT – DAY 0 – DAY 7 (Page 1 of 3)**

| **Protocol: CP-H5VLP-001 Telephone Follow-up Script** | | **Subject ID No. and Subject Initials:** | **PM, Day 1**  **Of Dose** | **1 Day after** | **2 Days after** | **3 Days after** | **4 Days after** | **5 Days after** | **6 Days after** | **7 Days after** |
| --- | --- | --- | --- | --- | --- | --- | --- | --- | --- | --- |
| **DAILY TEMPERATURE** | | **What is your oral temperature? Record (degrees Celsius) ►** |  |  |  |  |  |  |  |  |
| **Remind the subject to use their Memory Aid as a tool to answer the following questions** | | | | | | | | | | |
| **SYMPTOMS** | | **GRADING (Enter “0” if no symptom occurred)** | **PM, Day of Dose** | **1 Day after** | **2 Days after** | **3 Days after** | **4 Days after** | **5 Days after** | **6 Days after** | **7 Days after** |
| ► | Redness where the injection was given | 0 = None 1= More than 0 but NOT more than 20 mm 2= More than 20 mm but NOT more than 50 mm 3= More than 50 mm |  |  |  |  |  |  |  |  |
| ► | Swelling where the injection was given |  |  |  |  |  |  |  |  |  |
| ► | Pain where the injection was given | 0 = None 1= More than 0 but NOT more than 20 mm 2= More than 20 mm but NOT more than 50 mm 3= More than 50 mm |  |  |  |  |  |  |  |  |

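### The diary's first entry looks back 24 hours from the evening of the dose, so systemic symptoms from before the injection can be counted as Day 0 reactions

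*Protocol*

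**What the plan says.** **The form.** The Memory Aid (Protocol, Appendix A, Day 0 – Day 7) has a single instruction above all symptom columns: "entering the WORST grade for each symptom that you have had in the last day (24 hours". Its first column is headed "PM, Day 1 Of Dose". Section 5.1.5.3 uses Day 0 for the same evening, where subjects are "Requested to grade, on a daily basis from the evening of Day 0 through to Day 7 following each vaccination".

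**The endpoint.** Section 8.1.1.1 sets the start of the solicited-symptom window: "These signs and symptoms will be measured and reported by each study subject from the time of study vaccine administration".

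**How the data reach the site.** Section 5.1.5.3 says of the diary: "The completed MA will not be collected by the study site". The data come from telephone calls. Section 5.1.5.4 has staff record "the highest symptom grade experienced for each solicited local and systemic reaction from Day 0 to Day 1", then a second maximum for Day 2 to Day 7. The Appendix B script tells staff: "Remind the subject to use their Memory Aid as a tool to answer the following questions". Its symptom grid says nothing about counting only from the injection.

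**How the data are reported.** The sample 7-day safety summary (Appendix C) labels the Day 0 – Day 1 period as roughly the first 24 hours after vaccination. Its table of systemic reactions has a separate column for the evening of Day 0.

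**The concern.** For anyone vaccinated on the day of the entry, a 24-hour look-back from that evening must begin before the injection. A subject who had a headache or felt tired that morning, and follows the form literally, enters it in the first post-dose column. The systemic grid has no onset time, so the entry cannot later be separated from a reaction that followed the injection. The call then takes a maximum, so a pre-dose grade 2 would override a post-dose grade 1. Intensity is exposed as well as occurrence.

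The early period is where reactogenicity is of most interest. These counts feed the safety endpoint, compared with placebo by Fisher's exact test, and the 7-day tables read by the panel that permits escalation.

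**Working it through.** **1. Is the conflict in the text?** The first column is the evening of the dose (Appendix A; Section 5.1.5.3), the look-back is 24 hours (Appendix A), and the endpoint starts at administration (Section 8.1.1.1). With h hours from injection to entry and h below 24, the first look-back contains 24 − h pre-dose hours. The conflict therefore holds for every same-day injection.

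**2. Does a written step remove it?** The Day 0 procedures (Section 5.1.5.2) and the Day 21 procedures contain no pre-dose grading of the solicited symptoms. Section 5.1.5.4 makes no cut at the time of injection. Section 9.1.1 has a class of pre-dose events but does not link it to the solicited grid. No written step removes it.

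**3. Which items are exposed?** Redness, swelling and pain are asked about at the injection site, so at Dose 1 they cannot predate the injection. Temperature is a reading taken that evening. The recalled systemic items remain.

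**4. Share of the look-back that is pre-dose.** The protocol gives no clock times. Assume a 20:00 entry. The share is (24 − h)/24:

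| Injection | h | Pre-dose hours | Share |
|---|---|---|---|
| 09:00 | 11 | 13 | 54% |
| 12:00 | 8 | 16 | 67% |
| 15:00 | 5 | 19 | 79% |

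**5. The plan's own figure, for scale.** Section 11.3 gives the chance of seeing at least one reaction among 12 subjects as about 72% at 10% incidence and 46% at 5%. From 1 − (1 − p)^12: 1 − 0.90^12 = 71.8% and 1 − 0.95^12 = 46.0%. Both reproduce and are not in dispute.

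**6. Effect on the Day 0 rate.** Let b be the probability of a systemic symptom in the pre-dose hours, assumed independent of the true reaction rate p. The observed rate is 1 − (1 − p)(1 − b). The values of b are assumptions.

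| b | Expected pre-dose cases in 12 | Chance of at least one | True 10% reads as |
|---|---|---|---|
| 2% | 0.24 | 21% | 11.8% |
| 5% | 0.6 | 46% | 14.5% |
| 10% | 1.2 | 72% | 19% |
| 20% | 2.4 | 93% | 28% |

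If 10% to 20% of subjects have such a symptom in any 24 hours (also an assumption), proportional scaling gives b between 10% × 13/24 = 5.4% and 20% × 19/24 = 15.8%. One subject is 1/12 = 8.3 percentage points of a group.

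**7. Effect on the comparison.** Exact enumeration of the two-sided 5% Fisher test, 12 against 12, with the same b in both arms:

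| b | Type I error, true 10% vs 10% | Power, true 10% vs 60% |
|---|---|---|
| 0 | 0.25% | 64% |
| 5% | 0.67% | 56% |
| 10% | 1.11% | 50% |
| 20% | 1.65% | 39% |

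Type I error stays below 5%. The loss is in power.

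**8. Against the whole 7 days.** From injection to 20:00 on Day 7 is 7 × 24 + 11 = 179 hours (09:00 dose) or 7 × 24 + 5 = 173 hours (15:00 dose). The pre-dose hours add 13/179 = 7% to 19/173 = 11%.

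**The case against.** The strongest reply is that the diary is not the endpoint record. It is a recall aid for a staff interview, subjects are trained in clinic after the injection, and Section 8.1.1.1 states the right start. The Appendix B grid carries no 24-hour wording, and one of its health questions asks about changes since the vaccination. The endpoints also report relationship to vaccination, and Section 9.1.6 classes an event without plausible timing as probably not related. Before Dose 1 staff update history and medications and examine the subject. At Day 21 they ask about solicited events since Day 7. Fever and acute cold symptoms are temporary contraindications (Section 5.3.5).

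This stands in part. A reader might infer that every pre-dose symptom must be counted. The documents do not support that, because the interview or the relatedness assessment may catch some. But none of these steps is a graded pre-dose baseline, and none is tied to the grid. The interviewer is told to rely on the diary, whose wording is the problem.

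A reader might also infer that one arm is favoured or that escalation would be misdirected. Under randomisation and blinding between vaccine and placebo, the contamination should be similar in both arms. The systemic stopping criterion in Section 9.1.8 concerns reactions above grade 2 in more than 50%. Pre-dose symptoms that prevent normal activities seem unlikely in healthy volunteers attending for vaccination. Background symptoms over the following week enter both arms anyway, which is what the placebo group is for.

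**Conclusion.** The contradiction is real and limited. For the recalled systemic items on the evening of each dose, the form's look-back starts before the endpoint does, and no written step prevents a pre-dose symptom from being counted. It can inflate Day 0–1 systemic rates and intensities in the endpoint and the 7-day review tables, and it can dilute the contrast with placebo.

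The size is not known from the documents. It rests on the assumed clock times, background rates, independence and equal contamination of the arms. The reading of a true 10% rate as 14.5% to 28% applies to the first entry. It is an upper picture, because it supposes that every pre-dose symptom is carried through the interview. It should not be read as a distortion of the full 7-day result, where the added exposure time is about 7% to 11%.

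**What to change.** In Appendix A, word the first column as *worst grade since your injection today* and keep the 24-hour look-back for the later columns. Word the day-of-dose column of the Appendix B script the same way. Apply both changes at Dose 1 and Dose 2.

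This is a wording change to two sample forms, with no added visit, procedure or analysis. The documents do not say whether the forms have been printed; if they have, add a reprint. A symptom that began before the injection and continued after it would still be entered. Separating those would need a record of symptoms just before each dose, which is a further choice and is not needed to remove the contradiction.
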